## Abstract

Cardiovascular diseases are the leading cause of morbidity and mortality worldwide. High blood pressure in particular, continues to increase throughout the global population at an increasingly fast pace. The relationship between arterial hypertension and periodontitis has been recently discussed in the context of its origins and implications. Particularly relevant is the role of the periodontal microbiome linked to persistent local and systemic inflammation, along with other risk factors and social determinants of health. The present protocol will investigate/assess the association between periodontal disease and its microbiome on the onset of hypertension, within a cohort from Mexico City. One thousand two hundred twelve participants will be studied during a 60-month period. Studies will include analysis of periodontal conditions, sampling and sequencing of the salivary and subgingival microbiome, interviews on nutritional and lifestyle habits, social determinants of health, blood pressure and anthropometric measurements. Statistical associations and several classic epidemiology and machine learning approaches will be performed to analyze the data. Implications for the generation of public policy—by early public health interventions or epidemiological surveillance approaches—and for the population empowerment—via the establishment of primary prevention recommendations, highlighting the relationship between oral and cardiovascular health—will be considered. This latter set of interventions will be supported by a carefully planned science communication and health promotion strategy. This study has been registered and approved by the Research and Ethics Committee of the School of Dentistry, Universidad Nacional Autónoma de México (CIE/0308/05/2019) and the National Institute of Genomic Medicine (CEI/2020/12). The umbrella cohort was approved by the Institutional Bioethics Committee of the National Institute of Cardiology-Ignacio Chavez (INC-ICh) under code 13-802.

## 1. Introduction

High blood pressure (HBP) is the leading risk factor for myocardial infarction, cerebrovascular events, atherosclerosis, aortic aneurysms, peripheral arterial disease, heart failure, and chronic kidney disease, among other ailments. Hypertension (high blood pressure) is the most important cause of premature morbidity and mortality and has become a major public health problem (1). Almost 45% of the worldwide population is affected by it and the estimate increases with age in both sexes (2, 3). The etiology of most HBP is multifactorial, resulting from the interaction of renal, neural, cardiac, vascular, and endocrine mechanisms under the influence of genetic, epigenetic, as well as environmental, lifestyle and social factors (4). Additionally, pathophysiological alterations related to microbial dysbiosis, chronic inflammatory states, endothelial dysfunction, increased peripheral vascular resistance, oxidative stress, and immune system responses have been also associated to the incidence and prevalence of hypertension (5–8).

Periodontitis, in turn, is the most common periodontal disease (PD) in adults. Periodontitis has a high prevalence worldwide, it is known to affect around 30–50% of the population in developed countries (9). Periodontitis is a chronic inflammatory disease of infectious origins that has drawn increasing attention as a risk factor to develop hypertension and cardiovascular disease (CVD) (10, 11). Periodontitis is characterized by host-mediated microbe-associated inflammation that results in progressive destruction of the structures that support the teeth (gingiva, cementum, periodontal ligament, and alveolar bone), often leading to tooth loss (3). In particular, the role of the subgingival microbiota in the development of periodontitis, has been clearly identified (12, 13).

Periodontitis and HBP share specific social, economic and even some cardiovascular risk factors as endothelial dysfunction and systemic inflammation (14). However, recent evidence indicates that the association between periodontitis and hypertension may go beyond these factors and may indeed be causal in nature (7, 15, 16). A possible causal relationship has been proposed using Mendelian randomization—a reliable test of causality between risk factors and phenotypes—studied in the UK-Biobank and International Consortium for Blood pressure (ICBP)-Genome Wide Association Study (GWAS) datasets (including 750 000 participants) (16). This study confirmed a link between genetic variants to periodontitis (as approximate lifetime exposure to PD) and BP phenotypes (17).

Nevertheless, the exact mechanisms involved in the association between Periodontitis and HBP remain unknown (17). Clinical and experimental studies have suggested plausible mechanisms related to: local and systemic inflammation, the microbial effect on the vascular system, the host immune response and the specific type of cell activation (18). Certain studies have shown that PD is involved in the pathogenesis of systemic arterial hypertension, identifying the chronic inflammation associated with periodontitis as an independent link with the development and progression of CVD (19–22). Some mediators of chronic inflammation are able to promote subclinical atherosclerosis or endothelial dysfunction with consequences for hypertension. Direct oral microbial effects on the vascular system have also been suggested to affect BP via potential interactions of circulating bacteria with the vascular endothelium (23). Regarding the relationship existing on the triad: imbalance (dysbiosis) of the oral microbiome structure—periodontitis—cardiovascular disease, a number of cross-sectional, case-control, and cohort studies suggest that periodontitis is associated with CVD, specifically with atherosclerosis, by mechanisms involving microbial dysbiosis (24, 25).

To date the strongest hypotheses about the pathogenic route underlying this association suggest that the relationship is given by a progression of microbial dysbiosis. This, in turn, favors the development of periodontitis by generating chronic inflammation, disrupting the immune response (a phenomenon called immune subversion) and increasing the atherogenic potential (11, 18). Emerging experimental animal evidence indicates that immune system activation induced by a keystone periodontal pathogen (*Porphyromonas gingivalis*) promotes the development of hypertension, vascular inflammation, and endothelial dysfunction (3).

Despite this association between periodontitis and high blood pressure (26, 27), few longitudinal studies have been conducted to date, often with inconsistent results, as reported by Surma et al. (28). Some researchers have observed a temporal association between periodontitis and the incidence of HBP (6), but others have found no association between periodontitis and any risk conditions for cardiovascular disease (29–31). However, intensive treatment of severe periodontitis improves endothelial function by reducing systemic inflammation (decrease of proinflammatory markers and cytokines) in patients with and without other comorbidities (3, 23, 32).

The actual association between periodontal disease and hypertension is not new and several studies beyond the purely observational (such as the already discussed Mendelian randomization (16)) have ascertained it. However, one novel aspect of our study is that, in addition to analyze this association, we are interested in studying the role that the periodontal microbiome may be playing in both, initial and sustained infection; as well as in the modulation of the immune and inflammatory responses that lead to the systemic effects that are known (or hypothesized) to be behind the association between periodontal disease and hypertension.

After further confirmation via long-term longitudinal studies, periodontitis may represent a novel modifiable risk factor for hypertension (3). However, there are still profound gaps in our knowledge of what are the functional aspects that lead to dysbiosis in the oral subgingival microbiome, its relationship with periodontitis and other pathologies that have been associated with cardiovascular disease and hypertension (33). Longitudinal cohort studies are required to assess periodontitis exposure, associated risk factors, and the incidence of HBP. Along these lines, the purpose of this study is to contextualize the association between hypertension and periodontal disease, in particular by considering the role that microbial dysbiosis may have on each of these conditions, and on their interplay.

## 2. Scope of the Project

### 2.1. Main Goal of the Study

The main objectives of this study are: (i) to identify the subgingival microbiome, as well as the factors associated with periodontitis, (ii) to quantify its association with the incidence of hypertension and (iii) to analyze the triple association between the oral subgingival microbiome, the presence and extent of periodontal disease, and the development of hypertension in people aged 20 years and over that will be followed for a period of 60 months.

The primary endpoint is to determine the association of the subgingival microbiome profiles with the presence of hypertension and periodontitis. Secondary goals include the assessment of the relationship between periodontitis and hypertension in the socio-demographic context of the metropolitan population of Mexico City, as well as the characterization of the subgingival microbiome in periodontal health and periodontitis conditions of such study sample.

### 2.2. Specific Goals

Specifically we will reach the above mentioned goals through the following steps:

Estimating the prevalence of periodontitis in people aged 20 years and older at baseline in the cohort under study.Identifying differences in the distribution of known cardiovascular risk factors (age, gender, weight, physical activity, smoking habit, and stress) and social determinants of health (education, occupation, and marital status), in individuals with and without periodontitis at the beginning of the study.Estimating and assessing the impact on the quality of life of individuals with varying degrees of periodontitis at the beginning of the study.Identifying differences in the perceived need for dental treatment and the use of dental services between individuals with and without periodontitis at the beginning of the study.Studying the association between the subgingival microbiome profiles and the periodontal health conditions or periodontitis at baseline.Identifying whether cardiovascular risk factors and social determinants of health are associated with the risk for periodontitis and with the 60-month incidence of arterial hypertension in participants of the study.Analyzing the distribution of xerostomia, the use and functionality of removable prostheses, the presence of root remains, the number of present natural teeth, the number of teeth with caries, as well as the oral hygiene habits in persons with and without periodontitis.Identifying if there is any association between the 60-month incidence of hypertension and the baseline salivary and subgingival microbiome and the baseline presence of periodontitis.Analyzing the relative abundance of microbial species profiles in the salivary and subgingival microbiome and its relationship with arterial hypertension within a 60-month follow-up.Contrasting the epidemiological evidence of the relationship between periodontitis and hypertension with the findings of the analysis of the subgingival periodontal microbiome.

### 2.3. Hypotheses

The main hypotheses motivating the design of this project may be summarized as follows:

Individuals with periodontitis have an augmented risk of developing arterial hypertension than people without periodontitis, within a 60-month period controlling for: sex, age, smoking, and oral hygiene habits; as well as social determinants of health such as education, occupation, and marital status.The relative abundance of microbial species profiles in the subgingival periodontal microbiota of participants with and without periodontitis will be different.The relative abundance of microbial species profiles in the salivary and subgingival periodontal microbiota of participants that develop arterial hypertension will be different to that of the ones not developing HBP.

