#### 3.2.1. Participants and Recruitment

The study population is a sub-cohort of the participants in a cohort from the Mexico City metropolitan area (35). It is a prospective longitudinal study in which clinically healthy residents of Mexico City, between 20 and 50 years old are recruited to be evaluated every 2 years for a period of 10 years or until they develop hypertension. Anthropometric (weight, height and waist circumference), clinical and biochemical parameters (blood and urine laboratory tests with markers such as glucose, cholesterol, triglycerides, sodium and potassium, etc.), nutritional and lifestyle habits (physical activity, sleep quality, alcohol and tobacco consumption) and social determinants of health are assessed (Supplementary Material). All participants are measured periodically (every 2 years) by a battery of specific serum biomarkers of systemic inflammation. Participants will be contacted every 6 months via email or by telephone to assess their medical and dental history including treatment for hypertension and/or periodontitis, as well as any medication (including antibiotic treatment) used over the previous months (see Figure 1).

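### The adjustment set named in Hypothesis 1 drops weight, physical activity and stress, which the plan itself lists as known cardiovascular risk factors

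*Protocol article*

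**What the plan says.** Section 2.3 states the periodontitis hypothesis as a raised risk of hypertension "within a 60-month period controlling for: sex, age, smoking, and oral hygiene habits; as well as social determinants of health such as education", followed by occupation and marital status. The phrase introducing examples applies only to the social determinants. The clinical and lifestyle items before it (sex, age, smoking, oral hygiene habits) are given as a complete list.

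Section 2.2 will compare individuals with and without periodontitis on "known cardiovascular risk factors (age, gender, weight, physical activity, smoking habit, and stress", and on education, occupation and marital status. It also plans to identify whether "cardiovascular risk factors and social determinants of health are associated with the risk for periodontitis and with the 60-month incidence" of hypertension.

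Section 3.2.1 says the umbrella cohort records "Anthropometric (weight, height and waist circumference), clinical and biochemical parameters", the latter including "markers such as glucose, cholesterol, triglycerides, sodium and potassium", together with "lifestyle habits (physical activity, sleep quality, alcohol and tobacco consumption". Section 4 gives this study its own stage of interviews and anthropometric measurements.

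**The concern.** Periodontitis is not randomised here, so the claim that it raises the risk of hypertension depends on what is adjusted for. Section 1 itself says the two conditions share social, economic and some cardiovascular risk factors. Section 2.2 treats the cardiovascular risk factors as possible correlates of both exposure and outcome, which is what makes a variable a candidate confounder. Yet the only adjustment set named for this contrast leaves out three of the six factors on that list.

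If the analysis follows Section 2.3 as written, part of any periodontitis effect could belong to adiposity or inactivity. If the covariates are instead settled after the results are seen, the choice is open to the charge of being data-driven.

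**Working it through.** **1. The two lists side by side**

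| Factor in Section 2.2 | In the Hypothesis 1 set? | Recorded? |
|---|---|---|
| Age | Yes | Yes |
| Gender | Yes (sex) | Yes |
| Smoking | Yes | Yes (3.2.1) |
| Weight | No | Yes (3.2.1; anthropometry in 4) |
| Physical activity | No | Yes (3.2.1) |
| Stress | No | Not named in 3.2.1, but 2.2 plans to analyse it |
| Education, occupation, marital status | Yes, all three | Yes |

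**2. Does another section add the missing factors to this model?**

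- Section 3.5.1 lists oral health covariates only.
- Section 9.1.1 refers to covariates without naming any.
- Section 9.1.2 names alcoholism and smoking as risk factors, but for the oral variables. It mentions propensity scores a posteriori without listing variables.
- Section 9.2.4 brings in clinical, biochemical and lifestyle variables for the microbiome associations.
- Section 12.1 does not list this among the limitations.

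None of them does.

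**3. Illustrative size of the bias**

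The documents give neither the prevalence of a confounder by periodontitis status nor its effect on hypertension, so every input here is an assumption. For one omitted binary confounder with relative risk R for hypertension and prevalence a with periodontitis and b without:

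bias factor = (1 + a(R − 1)) / (1 + b(R − 1))

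- R = 2, 40% vs 30%: 1.40 / 1.30 = 1.08
- R = 2.5, 45% vs 30%: 1.675 / 1.45 = 1.16
- R = 3, 50% vs 30%: 2.00 / 1.60 = 1.25

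A wider grid (R from 1.5 to 2.5, prevalence 40-60% vs 30%) gives 1.04 to 1.31.

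**4. Can the study afford the extra terms?**

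Inputs from Section 3.3.1: 866 analysed, 10% exposed, incidence 21.5%, relative risk 2.4, 90% power, significance level 0.05, R² = 0.3, 40% dropout, 1,212 recruited. Assumptions: 21.5% is the incidence in the exposed, so the unexposed incidence is 0.215 / 2.4 = 0.0896; the test is two-sided.

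- *The plan's own figure.* The logistic sample-size formula for one binary covariate is N = [1.96·√(p̄(1−p̄)/B) + 1.2816·√(p₁(1−p₁) + p₂(1−p₂)(1−B)/B)]² / [(p₁−p₂)²(1−B)]. With B = 0.10, p₁ = 0.0896, p₂ = 0.215 and p̄ = 0.9 × 0.0896 + 0.1 × 0.215 = 0.102, it gives N = 864. That matches 866 without any R² term.
- *With the stated R² = 0.3.* 864 / 0.7 gives 1,235. No other reading of the inputs with R² = 0.3 came within 3% of 866. The nearest was 830 (one-sided, 21.5% taken as the unexposed incidence, 2.4 taken as an odds ratio).
- *Completers.* 1,212 × 0.6 = 727. Power at R² = 0.3 is about 74%. If further covariates raised R² to 0.4 (assumed), it would be about 69%.
- *Events.* 727 × 0.102 = 74. If 21.5% is instead the overall incidence, 727 × 0.215 = 156.

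**The case against.** The strongest reply is that Section 2.3 is not a model specification. It opens with "The main hypotheses motivating the design of this project may be summarized as follows", the analysis section closes no covariate list, and an article may leave the final list to a fuller document. This stands in part. A reader might infer that the plan fixes a set which excludes these variables and so leaves the effect confounded. The text does not go that far: it names a set, and nowhere says the others will be kept out. What remains is that the one set it names conflicts with its own risk-factor list. That is a conflict in the printed text, not a detail left for later.

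A reader might also infer that the omission inflates the relative risk by a known amount. It does not follow. Direction and size both rest on assumptions, and the planned adjustment for age, sex, smoking and education may absorb part of the bias. Even 1.25 is small beside the design relative risk of 2.4. It is not small if the truth lies near the lower end of the 1 to 2.74 range quoted in Section 3.3.1.

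Glucose is a weaker case than weight or activity. The plan never calls it a risk factor, Section 3.4.1 restricts entry to people without diabetes, and glucose may lie on the causal path. Alcohol is called a risk factor only for the oral variables.

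Finally, Section 2.1 places the periodontitis-hypertension relationship among the secondary goals. That lowers the stakes somewhat, but it is the first hypothesis, and the 1,212 participants are sized on it.

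**Conclusion.** The point holds as an internal conflict with consequences for bias. The adjustment set in Section 2.3 omits weight, physical activity and stress, which Section 2.2 calls known cardiovascular risk factors, and no other section puts them into the hypertension model. Following the named set can bias the periodontitis effect, plausibly upward, because adiposity and inactivity plausibly raise the risk of both conditions. The factor of 1.08 to 1.25 is an illustration on assumed prevalences and relative risks, not an estimate for this cohort. The case is firmest for adiposity and physical activity. Stress belongs with them by the plan's own list, and alcohol comes next. The documents do not support requiring glucose in the main model.

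**What to change.** Amend the control set in Section 2.3 so that it agrees with Section 2.2:

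- Add BMI or waist circumference and physical activity to the main model, plus stress and alcohol intake where recorded.
- Give a reason for any factor on the Section 2.2 list that is still left out.
- Use values measured at, or nearest to, the periodontal baseline. The first umbrella-cohort visit may be years earlier, since participants there are seen every 2 years for up to 10 years.
- Put glucose and baseline systolic pressure in a sensitivity model only, because either may lie on the causal path.

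For anthropometry, physical activity and alcohol this needs a sentence or two and no new data. The cost is some precision. With about 74 events at the low end, the additions should be few and economically coded. The R² = 0.3 allowance cannot be counted as cover for this, because 866 is reproduced only without it; the sample-size text should be corrected or the lower power acknowledged.

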## 3. Methods

### 3.1. Ethical Aspects

In accordance with the Regulation of the General Law of Health in Matters of Health Research, in the Second Title (Of the Ethical Aspects of Research in Human Beings) article 17, this research is classified among the Investigations with Minimum Risk, since no adverse effects have been reported from periodontal measurement on teeth (34). Written informed consent will be required. The confidentiality of the information will be ensured and each of the participants will be given a health diagnosis.

We must highlight that all participants will be given detailed information and recommendations about their individual health (blood pressure levels, lab tests and periodontal evaluation) immediately after every evaluation and referred to specialized treatment whenever needed. However, we should highlight that receiving medical and/or periodontal treatment will depend only on each participants' decision.

### 3.2. Study Population

This will be a cohort design, with the presence of periodontitis as an exposure factor for the development of hypertension (see Figure 1). This protocol was submitted and approved by the Ethics and Research Committee of the School of Dentistry, National Autonomous University of Mexico (SD-UNAM), the approval key is CIE/0308/05/2019 and the National Institute of Genomic Medicine (CEI/2020/12). The umbrella cohort was approved by the Institutional Bioethics Committee of the National Institute of Cardiology-Ignacio Chávez under code 13-802.

**Figure 1 F1:**
[figure not shown]
Outline of the study 60-month follow-up. Different scenarios are presented according to the participant role. *HBP*, High blood pressure; *SRM*, Semiannual remote monitoring; *APT*, Active periodontal treatment. The image generated by the authors was created with the *BioRender* App.

#### 3.2.1. Participants and Recruitment

The study population is a sub-cohort of the participants in a cohort from the Mexico City metropolitan area (35). It is a prospective longitudinal study in which clinically healthy residents of Mexico City, between 20 and 50 years old are recruited to be evaluated every 2 years for a period of 10 years or until they develop hypertension. Anthropometric (weight, height and waist circumference), clinical and biochemical parameters (blood and urine laboratory tests with markers such as glucose, cholesterol, triglycerides, sodium and potassium, etc.), nutritional and lifestyle habits (physical activity, sleep quality, alcohol and tobacco consumption) and social determinants of health are assessed (Supplementary Material). All participants are measured periodically (every 2 years) by a battery of specific serum biomarkers of systemic inflammation. Participants will be contacted every 6 months via email or by telephone to assess their medical and dental history including treatment for hypertension and/or periodontitis, as well as any medication (including antibiotic treatment) used over the previous months (see Figure 1).

